### Objectives and outcome measures/endpoints

The overall aim is to externally validate the multivariable risk prediction model we previously developed, recalibrating to the secondary care population if necessary and updating with additional predictor variables if necessary. The primary objectives are to:

Assess the external validity of the DRPTVL-UK model for predicting the risk of need for treatment or vision loss up to 2 years after referral in a hospital-based DR population by assessing model calibration, discrimination and net benefit.Evaluate whether recalibration of the baseline hazard or linear predictor (combination of predictor effects) improves predictive performance in an HES/surveillance clinic population and whether including additional predictors improves the model’s predictive performance in this population.

Secondary objectives are to:

Assess the DRPTVL-UK model’s external validity in the subgroup of patients with preproliferative DR (R2) or M1.Validate the model across several time points up to 2 years to assess whether it could be used to inform follow-up intervals after referral into HES or a surveillance clinic.

Parallel with the validation, there will be two consensus meetings of expert clinicians and patients to determine how the model can be implemented in practice and establish clinically meaningful thresholds for use.

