### Model recalibration and updating

If necessary, we will recalibrate the model to the HES population (eg, by updating the baseline survival function or recalibrating the linear predictor).^27^ In addition, we will investigate whether updating the model to include additional predictors that were not available in the development dataset improves the predictive performance. Visual acuity, early worsening, pregnancy and frequent ‘did not attend’, were identified as candidate predictors based on expert opinion and evidence evaluation.^21^ To update the model with additional predictors, flexible parametric models (Royston-Parmar models) will be fitted using a multivariable fractional polynomial approach to consider non-linear functions for continuous variables while using backward elimination for the additional predictors considered.^28^ We will use a p>0.157 as a proxy for selection based on Akaike information criterion.^29^ All predictors from the original model will be forced to remain in the model regardless of statistical significance, therefore, only the four additional variables will be tested. The predictive performance of the updated model will be evaluated using internal–external cross-validation^30^ in which the model is developed using the data from two hospitals and externally validated in the third. This is then repeated a total of three times, each time reserving a different hospital for external validation. Predictive performance will be evaluated in each ‘external’ hospital using the same measures of discrimination and calibration as previously described and will be summarised across the hospitals using random-effects meta-analysis. Predictive performance of the updated model will be compared with the original model.

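### Comparing the updated model only with the original does not isolate what the new predictors add; a refitted seven-predictor model is needed as comparator in the same cross-validation cycles

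*Protocol article*

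**What the plan says.** Under Objectives and outcome measures/endpoints, the second primary objective has two parts. The first is to "Evaluate whether recalibration of the baseline hazard or linear predictor (combination of predictor effects) improves predictive performance in an HES/surveillance clinic population"; the second is whether adding predictors helps in that population.

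Model recalibration and updating then describes the work:

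- Recalibration is conditional, with methods given as examples: "If necessary, we will recalibrate the model to the HES population (eg, by updating the baseline survival function or recalibrating the linear predictor". No validation scheme is attached to it.
- For the update, "flexible parametric models (Royston-Parmar models) will be fitted using a multivariable fractional polynomial approach to consider non-linear functions for continuous variables". Visual acuity, early worsening, pregnancy and frequent non-attendance are subject to backward elimination with p>0.157 as the criterion.
- "All predictors from the original model will be forced to remain in the model regardless of statistical significance". They stay in, but nothing says that their coefficients are held at the original values.
- "The predictive performance of the updated model will be evaluated using internal–external cross-validation": two hospitals for fitting, the third for testing, in rotation.
- The closing comparison is "Predictive performance of the updated model will be compared with the original model".

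Neither a recalibrated original nor a refitted seven-predictor model is named as a comparator anywhere in the article.

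**The concern.** The updated model can differ from the original in three respects at once: a new baseline, re-estimated effects for the seven original predictors (possibly with new fractional-polynomial forms), and the retained new predictors. One contrast cannot separate these, yet the objective asks about recalibration and new predictors separately.

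Some mismatch is plausible. The model was built in primary care data and is being moved to hospital eye services, and the plan itself allows for recalibration. At stake is the answer to the added-predictor half of a primary objective, which could err in either direction: a gain credited to variables that contribute nothing, or a real contribution understated.

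**Working it through.** **1. Does the plan's sizing fit a full refit?** Inputs from Sample size: event rate 0.05 per year, mean follow-up 3.23 years, Nagelkerke R² 0.15, 19 candidate predictors, shrinkage S = 0.9.

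- Events per patient: e = 0.05 × 3.23 = 0.1615.
- Null log-likelihood per patient: e ln(e) − e. Maximum Cox-Snell R² = 1 − exp{2[e ln(e) − e]} = 0.598.
- Cox-Snell R² = 0.15 × 0.598 = 0.0897.
- n = P / [(S − 1) ln(1 − R²/S)] = 19 / [(−0.1) ln(1 − 0.0897/0.9)] = 1809, with 1809 × 0.1615 = 292.2 events.

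The article states 1810 and 293, so its figure reproduces. With P = 4 (only the new terms estimated) the same formula gives 381. Sizing the step for 19 therefore fits re-estimation of a whole model rather than four terms added to a fixed linear predictor. This supports that reading but does not prove it.

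**2. What can the stated contrast show?** An illustrative simulation used three hospitals of 800 patients, leave-one-hospital-out, 60 replicates, exponential proportional hazards and seven standardised predictors. All effect sizes and shifts are assumptions. There was no backward elimination, no fractional polynomials and no difference between hospitals. Events averaged 418 to 580, against at least 360 expected in the article. The four new predictors had no true effect. Held-out C-statistics:

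| Assumed shift | Original | Recalibrated | Refitted seven | Seven + four | Last − original | Last − refitted seven |
|---|---|---|---|---|---|---|
| None | 0.708 | 0.708 | 0.704 | 0.701 | −0.007 | −0.003 |
| Baseline ×1.5 | 0.706 | 0.706 | 0.704 | 0.702 | −0.004 | −0.002 |
| Baseline ×1.5, moderate coefficient shift | 0.665 | 0.665 | 0.678 | 0.676 | +0.011 | −0.002 |
| Baseline ×1.5, larger coefficient shift | 0.620 | 0.620 | 0.684 | 0.682 | +0.062 | −0.002 |

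Differences are taken from the rounded values. In the same row order, observed/expected for the original was 1.00, 1.50, 1.39 and 1.37, and 1.00 for every other model. The calibration slope of the original was 1.01, 1.02, 0.78 and 0.55; it was 1.01 for the recalibrated model and 0.94 to 0.95 for seven plus four.

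A second simulation of the same layout (150 replicates, baseline ×1.5, effects 50–100% of the original ones) gave, for original versus seven plus four useless predictors, observed/expected 1.34 versus 1.00, slope 0.84 versus 0.95, and C 0.693 versus 0.691. Calibration looked better while discrimination fell slightly. Recalibration alone gave 1.01 for both observed/expected and slope.

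**3. When the new predictors do matter.** Each of the four was given a log hazard ratio of 0.15 in the first simulation.

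- Moderate coefficient shift with baseline ×1.5: original 0.665, refitted seven 0.677, seven plus four 0.691. The stated contrast gives 0.691 − 0.665 = +0.026, of which 0.677 − 0.665 = 0.012 is re-estimation and 0.691 − 0.677 = 0.014 is the new predictors.
- No shift: 0.706, 0.703 and 0.715. The stated contrast gives +0.009; the gain over the refitted seven is +0.012, so the contribution is understated by 0.003.

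**4. Why a recalibrated original alone is not enough.** Changing the baseline or multiplying the linear predictor by a positive slope leaves the ranking of patients unchanged, so C is identical in the first two columns. Only the refitted seven-predictor model removes the part of a C gain that comes from re-estimated coefficients.

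**The case against.** Several counter-arguments have force.

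- *The false gain is conditional.* This stands. A reader might infer that the updated model is bound to look better. It is not: C fell with no shift, with a baseline shift alone, and in the second simulation. Since the plan reports discrimination and calibration separately, corrected observed/expected with flat C would already point to recalibration. The contrast is uninterpretable for C mainly when coefficients shift.
- *Backward elimination guards against useless predictors.* In part. If all four are noise and the tests are independent single-parameter tests (an assumption), none is retained with probability 0.843⁴ ≈ 0.51, and 4 × 0.157 ≈ 0.63 are retained on average. The simulations omit this step. But elimination is in-sample selection at a lenient level, not a held-out gain in performance, which is what the objective asks about.
- *Recalibration lacks a held-out test.* A reader might infer that recalibration would then look perfect by construction. That does not follow: a baseline-only update does not force the slope to 1, and performance is calculated within each hospital before pooling, so a common recalibration need not be exact in each. Held-out recalibration also performed almost perfectly in the simulations, so this part matters little numerically.
- *The article may leave nested comparators to a fuller plan.* It does not exclude them, and the word 'only' is not its own. But it does fix one comparator, and that one does not match the two-part objective.

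**Conclusion.** The point holds in limited form. The one comparator the article names does not isolate the added-predictor question in the second primary objective. It can overstate the new predictors' contribution if the original transports imperfectly, or understate it if the original transports well. With useless predictors the apparent change in C ran from −0.007 to +0.062 across the assumed shifts, against −0.002 to −0.003 with the proper comparator.

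These figures show the mechanism and do not forecast this study: the article reports a C-statistic of 0.74 for the original but no coefficients, so the shifts cannot be checked. The reading that the seven effects are re-estimated rests on the description of the fit and on the sizing.

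A reader might go further and infer that the project will adopt a model that is harder to collect for no gain. The documents do not support that: elimination may drop the new variables, and Table 1 takes visual acuity at every visit and non-attendance from the patient administration system. External validation of the original model, the outcome, the sample size and data collection are unaffected. This is worth correcting before the updating analysis, but it does not put the study at risk.

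**What to change.** Replace the closing comparison in Model recalibration and updating with a nested set. In every internal-external cycle, use the same two hospitals for any fitting and test all four models on the third:

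1. the original as published;
2. the original with recalibrated baseline and/or slope;
3. a refitted model with the seven original predictors only;
4. the seven plus any retained new predictors.

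Repeat backward elimination and fractional-polynomial selection within each cycle where they apply. Judge recalibration by model 2 versus model 1 and the new predictors by model 4 versus model 3, on the held-out hospitals and with the measures already planned. Model 4 versus model 1 can still be reported as the overall effect of updating, without attributing it to the new predictors. Any advance illustration of a false gain should be given as a range that includes the no-shift case.

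The cost is a few extra model fits per cycle and a change of wording. No new data are needed.

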### Clinical benefit

We will also evaluate the clinical benefit of the model using decision curve analysis in which the net benefit of using the model at different threshold probabilities is plotted and compared with strategies of intervention for all (following up everyone more frequently) or intervention for no-one (no-one followed up more frequently).^31^

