## Abstract

**Introduction:**

The number of people with diabetes mellitus is increasing globally and consequently so too is diabetic retinopathy (DR). Most patients with diabetes are monitored through the diabetic eye screening programme (DESP) until they have signs of retinopathy and these changes progress, requiring referral into hospital eye services (HES). Here, they continue to be monitored until they require treatment. Due to current pressures on HES, delays can occur, leading to harm. There is a need to triage patients based on their individual risk. At present, patients are stratified according to retinopathy stage alone, yet other risk factors like glycated haemoglobin (HbA1c) may be useful. Therefore, a prediction model that combines multiple prognostic factors to predict progression will be useful for triage in this setting to improve care.

We previously developed a Diabetic Retinopathy Progression model to Treatment or Vision Loss (DRPTVL-UK) using a large primary care database. The aim of the present study is to externally validate the DRPTVL-UK model in a secondary care setting, specifically in a population under care by HES. This study will also provide an opportunity to update the model by considering additional predictors not previously available.

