The current length of follow-up intervals used within HES is based on the probability of disease progression from a study conducted in the late eighties^18^ and not based on the patient’s individual risk. We therefore aim to predict the progression of DR to treatment stage, to direct resources toward higher-risk patients so that they are followed up and treated before vision failure occurs. We propose that use of a validated risk prediction model will facilitate evidence-based decisions and thus reduce the chance of harm to higher-risk patients.

There are two recent systematic reviews of existing models for predicting the progression of DR among the DESP population.^15 19^ A review by this group of researchers found a total of 14 predictive model development studies of which 11 had been internally validated, 8 had been externally validated and only three without risk of bias.^15^ In a more recent review, there were 16 model development studies for an outcome of referable DR.^20^ Based on these two reviews, it was concluded that none of the existing models were intended for our target population (patients under care of HES/surveillance clinics) and none used the clinically important outcomes of interest (including contemporary treatment modalities and vision loss). Therefore, a prediction model that could be used to identify patients with a higher probability of requiring treatment or at high risk of loss of vision for HES was needed.

In brief, the DRPTVL-UK model was developed in anonymised, retrospective primary care data from IQVIA Medical Research Data (IMRD). From predictors identified in our systematic review,^15^ we selected a set of 19 clinically meaningful candidate predictors of DR progression using the Nominal Group Technique.^21^ A prediction model was then developed considering 15 of the 19 candidate predictors for inclusion based on availability in the dataset.^22^ After variable selection, the final model included seven predictors, namely (1) retinopathy stage, (2) glycated haemoglobin (HbA1c), (3) estimated glomerular filtration rate (eGFR), (4) total serum cholesterol, (5) systolic blood pressure and drug use of (6) insulin or (7) statins. The DRPTVL-UK model demonstrated moderately good discriminative performance (C-statistic=0.74) and very little optimism (0.004) in the internal validation due to the large sample size (13 691 patients).

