### DRPTVL-UK model

We previously developed and internally validated the DRPTVL-UK for the purpose of predicting the risk of vision loss and blindness or need for treatment in patients with referable DR. The model had good discrimination (C-statistic=0.74) and very little optimism in the internal validation. The model^22^ was developed in a primary care population and now needs external validation in the HES/surveillance clinic population, in which it is intended to be used.

The DRPTVL-UK model was developed using Cox regression and later refitted using a flexible parametric approach to obtain the baseline hazard function over time. The model can be used to predict the absolute risk of progression from referable DR to treatment or vision loss occurring within a 2-year period, based on an individual’s risk factor values. Thorough evaluation of the model’s external validity and net benefit is now required to establish whether the model is suitable for use in clinical practice in HES/surveillance clinics.

The DRPTVL-UK model can also be used to predict the time at which an individual reaches a particular risk threshold (to be agreed in a consensus meeting of clinical experts and patients planned after final analysis) which may be useful for determining appropriate follow-up intervals after referral to HES/surveillance clinics. This will be evaluated as a secondary objective.

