### External validation of the DRPTVL-UK model

The DRPTVL-UK model will be used to obtain the predicted probability of the outcome over time for every participant within each of the three trusts. Predictive performance of the model will be assessed using measures of discrimination (Harrell’s C-statistic and time-dependent C-statistic), calibration (calibration slope, ratio of observed to expected probabilities, calibration plots at multiple time points up to 2 years) and net benefit using decision curves. Performance measures will be calculated within each hospital and then pooled on an appropriate scale using random effects meta-analysis to account for clustering by hospital.^26^

As another potential use of the model would be to determine appropriate follow-up intervals based on the individual’s risk, it will also be crucial to ensure that the model performs well for predictions at all time points up to 2 years to ensure risk predictions are accurate over time. Therefore, we will also evaluate calibration performance at multiple time points. In addition to this, we will look at the predictions over time (predicted survival curves) and compare these to the observed survival curves for risk groups and other meaningful groupings, for example, DR grade.

In addition to external validation of the model in the whole sample, we will also validate the model within the subgroups of R2/M1 patients to see how well it performs in each.

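### Net benefit is set against following up everyone or no-one more often, not against current triage by retinopathy stage, so it cannot show an improvement on that triage

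*Protocol article*

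**What the plan says.** On current practice, the abstract's Introduction states: "At present, patients are stratified according to retinopathy stage alone, yet other risk factors like glycated haemoglobin (HbA1c) may be useful". The main Introduction adds that present follow-up intervals are "not based on the patient’s individual risk". The abstract concludes that "a prediction model that combines multiple prognostic factors to predict progression will be useful for triage in this setting to improve care".

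Net benefit has a central role. The first primary objective (Objectives and outcome measures/endpoints) is to be met "by assessing model calibration, discrimination and net benefit". The section on the DRPTVL-UK model says that thorough evaluation of external validity and "net benefit is now required to establish whether the model is suitable for use in clinical practice in HES/surveillance clinics".

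The Clinical benefit section then gives the strategies for the decision curve: the model is "compared with strategies of intervention for all (following up everyone more frequently) or intervention for no-one (no-one followed up more frequently". No third strategy is named.

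Two other planned analyses come near the question:
- External validation of the DRPTVL-UK model: predicted survival curves are to be set beside observed ones, to "compare these to the observed survival curves for risk groups and other meaningful groupings, for example, DR grade". The same section also validates the model within R2/M1 patients.
- Model recalibration and updating: "Predictive performance of the updated model will be compared with the original model".

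Retinopathy stage is the first of the seven predictors listed in the Introduction and under Predictor variables. The footnote to Table 1 ranks five grades and says which eye's grade enters the analysis.

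**The concern.** Everyone and no-one are the usual reference lines of a decision curve, but by the article's own account neither is what hospitals do now. Patients are already sorted by stage, and the case for the model is that further factors sort them better. Because stage sits inside the model, part of any gain over the two reference lines is gain that stage alone would deliver. The planned curve cannot separate the two parts.

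At stake is the reading of a favourable curve. Under Clinical consensus, the decision-curve results go to the expert panel that will discuss implementation, and the dissemination plan includes an electronic calculator. The panel would see no curve for current triage. It could credit HbA1c, eGFR, cholesterol, blood pressure and drug use with a benefit that comes from stage.

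**Working it through.** The article gives no net-benefit figure to reproduce. The check asks when a rule that uses stage alone beats both planned defaults. If it does, so can a model that adds nothing to stage.

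**Inputs.**
- From Sample size: an event rate of 0.05 per year gives a 2-year risk π = 1 − exp(−0.05 × 2) = 9.5%.
- The same section expects 15% within 3 years. I use 15% as an assumed upper value for the 2-year risk.
- Assumed, because the article gives none: share flagged by stage f = 20%, 30%, 40%; risk ratio of flagged to unflagged RR = 2, 3, 4; threshold t = 10%, 15%, 20% (thresholds are left to consensus).

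**Formulas.** Risk in unflagged patients r0 = π / (1 − f + f·RR); in flagged patients r1 = RR·r0; w = t/(1 − t).
- Stage only: NB = f·[r1 − (1 − r1)·w]
- Everyone: NB = π − (1 − π)·w
- No-one: NB = 0

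Stage-only NB is above 0 exactly when r1 > t. Stage only minus everyone equals −(1 − f)·[r0 − (1 − r0)·w], which is above 0 exactly when r0 < t. So stage alone beats both defaults whenever the threshold lies between r0 and r1.

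**One case.** π = 0.095, f = 0.30, RR = 3, t = 10% (w = 1/9).
- r0 = 0.095/1.6 = 0.0594; r1 = 0.1781
- Stage only: 0.30 × (0.1781 − 0.8219/9) = 0.0260, or +26.0 per 1000
- Everyone: 0.095 − 0.905/9 = −0.0056, or −5.6 per 1000
- No-one: 0

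A calibrated model whose other six predictors added nothing would reproduce this rule. The planned curve would show a gain of 26.0 per 1000; the gain over stage would be 0.

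**Across thresholds** (f = 30%, RR = 3; net benefit per 1000; margins from unrounded values):

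| 2-year risk | Threshold | Stage only | Everyone | No-one | Stage minus better default |
|---|---|---|---|---|---|
| 9.5% | 10% | 26.0 | −5.6 | 0 | +26.0 |
| 9.5% | 15% | 9.9 | −64.7 | 0 | +9.9 |
| 9.5% | 20% | −8.2 | −131.2 | 0 | −8.2 |
| 15% | 10% | 60.4 | 55.6 | 0 | +4.9 |
| 15% | 15% | 46.3 | 0.0 | 0 | +46.3 |
| 15% | 20% | 30.5 | −62.5 | 0 | +30.5 |

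Over all 2 × 3 × 3 × 3 = 54 combinations, the margin is positive in 41 and runs from −32.1 to +58.5 per 1000.

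**Do the other analyses fill the gap?**
- Survival curves grouped by grade check calibration within grade. They do not compare two ways of choosing patients.
- The updated-versus-original comparison keeps every original predictor in both models, so their value beyond stage is not tested.
- In R2/M1 patients, stage has a C of 0.5 within any single grade, so discrimination there would reflect the other six predictors. This is informative, but it covers only part of the grade range and yields no stage-based strategy for comparison.

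**The case against.** The strongest counter-argument is the R2/M1 validation. A model that added nothing to stage would show no discrimination within a single grade, so the plan has some means of exposing it. That stands, with limits. The Objectives can be read as one combined R2-or-M1 group, in which some variation in stage remains, while the external validation section speaks of performance in each. The Limitations section warns that subgroups are small. No net-benefit contrast follows.

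Second, superiority over stage-based triage is not a listed objective, implementation is left to a panel, and the article says further research on clinical and economic impact may be needed. A reader might infer that the protocol promises to show superiority; it does not. It does tie net benefit to suitability for practice and argues from the shortcomings of stage-only triage, so the missing contrast still matters.

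Third, six non-stage predictors were in the final model after variable selection in 13 691 patients, so a model adding nothing at all is unlikely. That is fair, but selection in a sample of that size does not say how much they add.

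Fourth, this is a condensed article, and a fuller plan may add strategies. If so, the point is met there. But the article does more than stay silent: it names the strategies and leaves out the practice it wants to improve on.

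**Conclusion.** The point holds for net benefit. As planned, the decision curve cannot show whether the model improves on current triage, and no other planned analysis supplies that contrast. Calibration and discrimination of the model itself are unaffected, as are the sample-size figures.

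Three stronger readings are not supported:
- That the study can say nothing about value beyond stage. The R2/M1 validation says something.
- That a model adding nothing would always beat both defaults. It could: stage alone did in 41 of 54 assumed scenarios, and a poorly calibrated model could fall below them.
- That the apparent benefit is inflated by a fixed, large amount. The margin depends strongly on the threshold and in these scenarios is largest where the threshold is near the overall risk, so a single figure at 10% would mislead.

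All net-benefit figures rest on assumed stage mix, risk ratios and thresholds. They show that the problem can arise, not how large it will be in these hospitals.

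**What to change.** In the sections on external validation and clinical benefit, add a stage-only comparator:

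1. Predict 2-year risk from the Table 1 grades alone. This avoids inventing a rule that maps grade to follow-up, which the article does not define.
2. Estimate it in two hospitals and evaluate it in the third, using the internal–external scheme already planned for the updated model. Fitted and tested on the same data, it would have an unfair advantage over a model brought in from primary care. Two hospitals should give about 2 × 200 × 4 = 1600 patients and, at 15% within 3 years, 240 events, against four coefficients for five grades.
3. Report model minus stage-only, and recalibrated model minus stage-only, for net benefit across the consensus threshold range and for C. Give confidence intervals and pool across hospitals.
4. Base any statement of improvement over current triage on that contrast. Keep everyone and no-one as reference lines.

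The cost is a little more analysis and probably a smaller apparent benefit. No new data and no change in sample size are needed, because grade is already collected.
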